### Implementation {16c}

Once patients consent study participation baseline assessment will take place. Afterwards, a member of the study team will access the web-based randomisation application. The allocation result will be displayed immediately to the study team member and will be logged in a database. Patients will be informed and receive written information about the randomisation result. The attending physician will be informed about the result and the next steps to be taken by post, to ensure data privacy, or in person, if the patient enrolment took place in the practice.

## Assignment of interventions: blinding

### Who will be blinded {17a}

Due to the nature of the study and the required involvement of PCPs, blinding of patients and the study staff directly involved in the trial is not possible. The statistician will be blinded until database lock after (blinded) data review and finalisation of the statistical analysis plan.

### Procedure for unblinding if needed {17b}

Only the trial statistician will be blinded. We do not anticipate a situation where unblinding to the analysis will be needed. In the event the trial statistician is no longer blinded, another statistician will perform the analysis, if feasible.

## Data collection and management

### Plans for assessment and collection of outcomes {18a}

Baseline data for PCPs will be collected on paper, immediately after signing informed consent and during a personal appointment with the study team. Baseline assessments for PCPs will contain demographic (gender, age, work experience, hours of work per week) and practice characteristics (practice size, location (urban/rural) and type (individual/group practice)). The planned time points for collecting patient data are summarised in Table 1, while SPIRIT item 12 provides detailed information on primary and secondary outcomes as well as process evaluation. In addition to outcome data, the following data will be collected from patients at baseline (t0), after 6 months (t1) and 18 months (t2):Demographics: gender, age, household size, years of educationMain diagnosis for study inclusion: musculoskeletal, oncologic or psychological conditions or the PCSEmployment characteristics: employment status, hours of employment per weekJob satisfaction: assessed on a 1–10 Likert scaleReason for sick leave: musculoskeletal, oncological, psychological or PCSSymptoms of anxiety and depression: measured with the German version of the Hospital Anxiety and Depression Scale (HADS-D) [32], which is widely used and internationally accepted as a screening tool for anxiety and depression in people with physical health conditions and disorders. The scores of the two subscales (anxiety and depression) are ranging from 0 to 21, with higher scores indicating more severe symptoms.

All patient data will be collected on paper. Data collection will take place during personal appointments or a telephone call with a member of the study team. In this case, patients will receive the questionnaires in advance by post. The process evaluation will use a mix of data (see SPIRIT item 12).

Patients in the intervention group will answer further questionnaires directly in the digital platform Cankado [24], again the WAI [20], and the Würzburger Screening [33], which helps to decide to what extent a person has occupational problems and needs occupationally oriented and vocational rehabilitation services as well as further medical anamnesis questionnaires. However, these data will be only used for decision-making in the CC and will not be evaluated separately by the study team.

### Plans to promote participant retention and complete follow-up {18b}

Patients will be contacted by the study team (by telephone or mail) before each data collection point, to encourage retention and the completion of follow-ups. Contact will be arranged flexibly by telephone and/or mail according to the preference of the patient. The importance of data collection for the success of the study will be emphasised in both groups in order to motivate patients to continue participation at follow-up. Data collection will be completed by a research assistant. Appointments will be arranged flexibly and can take place by telephone or at a preferred location (e.g. the primary care practice or the patient’s home), to make it as easy as possible for patients to participate in data collection. As part of the process evaluation, the reasons for and numbers of participant dropouts will be monitored.

### Data management {19}

All data, except for SF-36 [21, 22], data collected by the health insurance companies and the dates of data collection are entered using the FormPro software for automatic recognition and recording of completed questionnaires [34] and double-checked by a study assistant. All other data is entered manually by a study assistant and double-checked. Regarding the query management, the study team will take care that the questionnaires are completed correctly during data collection. Discrepancies that will arrive nevertheless during paper-based data collection will be discussed by the study team and, if necessary, declared as missing. The data preparation will be documented in the dataset. A data management plan has been developed based on the European General Data Protection Regulation (GDPR) 2018. Only the research team at the University of Marburg will have access to the collected data. Personal data will be stored on the server at the University of Marburg, password-protected, and separate from the research data as well as in a locked closet in the office of the research team. Personal data will be deleted 10 years after the end of the study. The collection of research data via the Cankado communication platform [24] also follows the GDPR and data will be stored on a server in Germany. During the CCs, no personal data, except for the questionnaires that patients answer on the platform, will be made available to the attendants. This data will be used to make appropriate treatment (MT/NMSM) recommendations in the context of the CC and will not be stored by the study team. All other research-relevant data from Cankado [24] will be exported anonymously after the study is completed and stored password-protected on the server at the University of Marburg. The data will be stored separately from the other research data collected. There will be no linkage between the regular research data and the data collected by Cankado [24]. The interviews will be recorded and transcribed verbatim. Interview data will be pseudonymised. The transcription will be carried out either by the study team itself or by an external transcription agency. The recordings of the interviews and the final transcription will be stored on the server of the University of Marburg.

### Confidentiality {27}

All data collected will be handled confidentially and in accordance with the consent provided by participants. For further information on data management see SPIRIT item 19.

### Plans for collection, laboratory evaluation and storage of biological specimens for genetic or molecular analysis in this trial/future use {33}

N/a This trial will not involve collection, laboratory evaluation, and storage of biological specimens.

## Statistical methods

### Statistical methods for primary and secondary outcomes {20a}

The participant flow will be reported according to the CONSORT guideline [23], which will show withdrawals and drop-outs. PCP and patient characteristics as well as outcomes, and process evaluation data will be descriptively reported using mean values and standard deviations for normally distributed data and median and range for not normally distributed data. Categorical data will be presented in amount and percentage.

All analyses will be performed using a modified intention-to-treat approach on both primary and secondary outcomes. According to a treatment policy estimand strategy, all participants without missing outcome data will be analysed according to their randomised treatment assignment. However, we will exclude cases with missing data due to dropout or loss to follow-up from the main analyses (for details, see item 20c).

For the primary outcome, we will fit a linear regression model with the cumulative sum of sick leave days during the period between t1 and t2, reported by health insurance, as a dependent variable and the treatment indicator as an independent variable, adjusted for sex, age, baseline number of sick leave days and baseline WAI [20] to control for differences between groups at baseline despite randomisation. Additionally, PCP IDs will be included as random intercepts in order to adjust for influence from stratified randomisation [35]. We will report the primary outcome as adjusted between-group mean differences with a 95% confidence interval. We will conduct analogue analyses for the secondary outcomes of self-reported sick leave days, work ability (WAI, 20) and health-related quality of life (SF36, 21, 22).

Interview data will be transcribed and qualitatively analysed using thematic analysis [36].

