## Methods: participants, interventions and outcomes

### Study setting {9}

Recruitment will take place in the setting of primary care in the state of Hesse (Germany). The aim is to recruit 59 PCPs from urban and rural areas in the regions of Frankfurt, Marburg-Biedenkopf as well as central and northern Hesse in the study. Each PCP will be asked to recruit six patients from their practice.

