## Assignment of interventions: allocation

### Sequence generation {16a}

Eligible and consenting patients will be randomised after baseline assessment with a 1:1 allocation stratified by primary care practice and using permuted blocks of six (as this is the number of patients to be recruited in the practices).

Prior to the commencement of the trial, an algorithm was used to create random sequences and discarded if they were not balanced (1:1) or too trivial, to ensure concealment for as long as possible (till the randomisation of the last patient). One of the random sequences was then randomly assigned to each practice to be recruited. This procedure was carried out by an independent researcher who was not involved in the conduct of the study in any other way.

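### The listed covariates leave out main diagnosis and name no baseline SF-36 for the SF-36 model; this causes no bias, but both are collected and adding them could improve precision

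*Protocol article*

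**What the plan says.** All references are to the protocol article.

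- **Primary model (section 20a).** A linear regression of cumulative insurer-reported sick leave days from t1 to t2 on treatment, "adjusted for sex, age, baseline number of sick leave days and baseline WAI [20] to control for differences between groups at baseline despite randomisation". It continues: "PCP IDs will be included as random intercepts in order to adjust for influence from stratified randomisation".
- **Secondary outcomes (section 20a).** "We will conduct analogue analyses for the secondary outcomes of self-reported sick leave days, work ability (WAI, 20) and health-related quality of life". The article does not say whether each outcome's own baseline replaces or joins the listed covariates.
- **Main diagnosis.** Section 18a lists main "diagnosis for study inclusion: musculoskeletal, oncologic or psychological conditions or the" post-COVID-19 syndrome among the data collected from patients. Section 20b uses it, with age and gender, to look for effect heterogeneity. It is not a stratification factor.
- **Baseline outcome values.** Section 18a implies that outcome data are collected at t0, t1 and t2 (Table 1 is not available to confirm this). Section 12 collects sick leave for the six months before baseline from both the insurer and the patient.
- **Randomisation (section 16a).** The stratum is the practice: "One of the random sequences was then randomly assigned to each practice to be recruited". Section 9 sets the quota per physician: "Each PCP will be asked to recruit six patients from their practice".

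**The concern.** The stated purpose of the adjustment is to deal with baseline differences that remain after randomisation. The trial pools four different conditions, and nothing in the design balances them between arms. Of the three factors that section 20b treats as possible effect modifiers, age and sex are in the primary model and diagnosis is not. No reason is given.

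For self-reported sick leave and WAI, the covariate list already holds a baseline counterpart. For SF-36 it does not. If the list is carried over unchanged, SF-36 at t2 is adjusted for baseline WAI and sick leave days but not for baseline SF-36.

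The random intercept is labelled by PCP, but its stated purpose is to reflect a randomisation stratified by practice. Section 18a records whether a practice is individual or group, so the two identifiers could differ.

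What is at stake is the width of the confidence intervals. The section on trial status says recruitment was stopped early for low numbers, so precision can no longer be gained by enrolling more patients.

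**Working it through.** **1. The plan's own figures.** Inputs from section 14: difference 34 days, SD 90, two-sided 5%, power 90%, 15% loss.
- Two-sample t-test: n = 148.2, rounded up to 149 per group; power at 149 is 90.2%.
- 149 / 0.85 = 175.3, rounded up to 176 per group; 2 × 176 = 352.
- 352 / 6 = 58.7, rounded up to 59.

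All reproduce. They come from an unadjusted test, so they do not depend on the covariate list.

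**2. Adding main diagnosis.** Assumption: diagnosis explains a further share R² of the variance left after the listed covariates. The ratio of standard errors is √(1 − R²):
- R² = 0.03: √0.97 = 0.985, a fall of 1.5%
- R² = 0.05: √0.95 = 0.975, a fall of 2.5%
- R² = 0.10: √0.90 = 0.949, a fall of 5.1%

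In days, with 149 per group and SD 90, SE = 90 × √(2/149) = 10.43.

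| Partial R² | SE (days) | Power for 34 days |
|---|---|---|
| 0 | 10.43 | 90.2% |
| 0.01 | 10.37 | 90.4% |
| 0.02 | 10.32 | 90.7% |
| 0.05 | 10.16 | 91.5% |
| 0.10 | 9.89 | 92.9% |

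This takes 90 days as the residual SD after the four listed covariates. If they already bring it below 90, power starts higher and the gain in power is smaller, but the SE ratios stay the same. In patients, the gain is about R² × 298 analysed (2 × 149): 9 at R² = 0.03 and 30 at R² = 0.10.

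The article does not give the number finally recruited. Purely as an illustration, with 75 analysed per group, power would go from 63.2% to 65.5% (R² = 0.05) or 67.8% (R² = 0.10).

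**3. Adding baseline SF-36 to the SF-36 model.** Assumptions: correlation ρ of 0.4–0.7 between baseline and t2 SF-36; correlation q of 0.5–0.7 between baseline WAI and baseline SF-36; and WAI predicts t2 SF-36 only through baseline SF-36. The SE ratio, with against without baseline SF-36, is √[(1 − ρ²) / (1 − ρ²q²)].
- Smallest gain, ρ = 0.4, q = 0.7: √(0.84 / 0.9216) = 0.955, a fall of about 5%
- Largest gain, ρ = 0.7, q = 0.5: √(0.51 / 0.8775) = 0.762, a fall of about 24%

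The variance falls by 9% and 42% respectively.

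**4. PCP or practice as random intercept.** With one recruiting PCP per practice, the two models are identical. For the other case, a simulation used 50 practices of six patients (300 patients, close to the 298 planned for analysis), balanced within practice, with about half the practices having two recruiting PCPs. There were 150 replicates per setting. The mean SE with PCP, relative to practice, was:
- ICC 0.02: 1.0007
- ICC 0.05: 1.0053
- ICC 0.10: 1.0097

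The loss is therefore between nothing and about 1%.

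**The case against.** Three arguments for the plan carry weight.

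- **Diagnosis is a choice, not an obligation.** It is not a stratification factor, and leaving out a prognostic covariate does not bias a linear comparison between randomised groups. Prior sick leave and WAI may already carry part of its effect. The article gives no evidence that diagnosis is strongly prognostic, and early closure makes chance imbalance likelier for any unlisted variable, not only this one. All of this stands, so a reader should not infer a biased or underpowered primary analysis. The planned power needs no covariates at all.
- **An analogous model need not have the same covariates.** The primary model adjusts for the outcome's baseline counterpart, so the natural analogue for SF-36 includes baseline SF-36. A reader might infer that the plan denies SF-36 its own baseline, but the article does not say so. What remains is that the text supports two different models for a named secondary estimand. Section 17a says a statistical analysis plan will be finalised after blinded data review, and that plan may settle it.
- **PCP and practice are used as one unit.** The article speaks of 59 PCPs (section 9) and of 59 PCP practices (Discussion), with six patients for each. Recording practice type does not show that two PCPs of one practice recruit. A reader might infer that the wrong cluster costs precision, but the counts and the simulation do not support that. Only the label is left to tidy.

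None of this argues against using data that are already collected.

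**Conclusion.** The point holds as a low-cost improvement, not as an error. The listed primary model omits main diagnosis, and the SF-36 model does not name its own baseline.

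For diagnosis the gain is modest: 1.5–5% of the SE at an assumed partial R² of 0.03–0.10, with power at the planned size rising from 90.2% to 92.9% at most. For SF-36 it could be material, about 5–24% of the SE under the assumed correlations. But SF-36 is a secondary outcome, and the loss exists only if the identical covariate list is intended. The PCP label matters only where several PCPs of one practice recruit, and even then by about 1% of the SE at most. The documents supply none of the R² values, correlations or ICCs, so these ranges show plausible size and are not estimates for this trial.

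**What to change.** In section 20a or the statistical analysis plan, before the statistician is unblinded:

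1. Keep sex, age, baseline sick leave days and baseline WAI in every model. Replacing them in the secondary models would discard planned covariates.
2. Add main diagnosis (four categories) to the primary and secondary models.
3. State that each secondary model also includes the outcome's own baseline: the corresponding baseline sum score for SF-36, and self-reported baseline days for self-reported sick leave. Baseline WAI is already there. State whether the baseline sick leave days in the common list come from the insurer or the patient.
4. State that the random intercept is the practice used as the randomisation stratum.

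The cost is a few sentences, three degrees of freedom for diagnosis and one for each added baseline value, with no new data collection. One check is needed. Section 20c excludes patients with missing values on any model variable, so the completeness of baseline SF-36, self-reported days and main diagnosis should be confirmed in the blinded data review. These are taken before randomisation with the study team, so few gaps are to be expected.

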### Interim analyses {21b}

N/a. No formal interim analyses are planned.

### Methods for additional analyses (e.g. subgroup analyses) {20b}

Subgroup analysis will be performed for the intervention group based on regression models according to age, gender and main diagnosis for study inclusion to determine treatment effect heterogeneity.

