### Objectives {7}

The overall objective is to assess the effectiveness of the developed platform-based case management approach (intervention condition) for rehabilitation care planning compared to treatment/care planning as usual (control condition).

The primary estimand is defined by the following attributes:Treatment condition: assignment to platform-based case management approach (intervention condition) for rehabilitation care planning compared to treatment/care planning as usual (control condition) including the effects of withdrawal from rehabilitation care.Target population: adults aged 40 to 60 years with a minimum of 4-week (20 workdays) work disability due to musculoskeletal, oncologic or psychological conditions or the post-COVID-19 syndrome (PCS) within the last 6 months prior to study inclusion (patient-reported information) and a high risk of early retirementEndpoint: cumulative sick leave days, health insurance data, during the period of 12 months after completion of the treatment (t1 to t2).Intercurrent events and strategies to address them: plausible and important intercurrent events include the patients’ withdrawal from the rehabilitation due to any reason, are addressed in the treatment condition attribute and handled with the treatment policy strategy.

The secondary estimands differ from the primary only in regard to the endpoints: self-reported cumulative sick leave days during the period of 12 months after completion of the treatment (t1 to t2); work ability, as measured by the Work Ability Index (WAI, German version) [20] and the health-related quality of life, as measured by the Short Form 36 Health Survey (SF-36, German version) [21, 22] 12 months after completion of the treatment (t2).

We also aim to describe the delivered process in terms of adherence, use of treatments (MT/NMSM), implementation of the intervention, treatments (MT/NMSM) recommended on the digital platform as well as involvement of a social worker. Moreover, facilitating and hindering factors that influence the success of the intervention and to identify adaptations that are necessary for a successful implementation will be investigated qualitatively as a part of the process evaluation.

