### Sample size {14}

Based on a systematic review of workplace interventions to prevent work incapacity [27], a difference of 34 days of incapacity to work (12-month period between t1 (assumed end of treatments) and t2) between the intervention and control group is assumed and applied for sample size calculation. A sample size of 149 patients in each group will have 90% power to detect a difference in means of 34 days of sick leave assuming that the common standard deviation is 90 days using a two-group *t*-test with a 5% two-sided significance level. Assuming that about 15% will be lost to follow-up or withdraw from the study, 352 participants have to be included. If a PCP would recruit six participants, about 59 PCPs must participate in the study. Sample size calculation was performed using R: A Language and Environment for Statistical Computing [28] and the package pwr [29]. The number of patients to be recruited per practice (*n* = 6) is based on feasibility and experience regarding the reasonableness for participating practices.

Participating in the interview study, as a part of the process evaluation, will be optional. The sample size for interviews will depend on data saturation [30]. We plan on interviewing 12 to 25 PCPs and patients each. Persons involved in the CC (public health physician, case administrator, social worker) will also be invited for the interview.

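### Subgroup regressions confined to the intervention group cannot separate treatment effect heterogeneity from prognosis

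*Protocol article*

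**What the plan says.** Section {20b} is a single sentence. It fixes the population and method, "Subgroup analysis will be performed for the intervention group based on regression models according to age, gender and main diagnosis for study inclusion", and the purpose, "to determine treatment effect heterogeneity". It mentions neither control patients nor an interaction with treatment.

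The only model that contains treatment is the primary one in {20a}. It has "the treatment indicator as an independent variable, adjusted for sex, age, baseline number of sick leave days and baseline WAI", plus a random intercept for the primary care physician. It contains no main-diagnosis term and no interaction. The effect scale is given there too: "We will report the primary outcome as adjusted between-group mean differences with a 95% confidence interval". Section {7} likewise defines the objective as a comparison of the platform-based approach with care planning as usual.

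The sections on trial design {8}, process evaluation (under {12}) and data collection {18a} use the term intervention group for one of the two arms. Section {20c} uses it more loosely, as the variable by which a baseline table is split.

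**The concern.** Treatment effect heterogeneity means that the intervention-minus-control difference varies between subgroups. A regression of sick leave on age, gender and diagnosis within the intervention arm contains no such difference. Patients with musculoskeletal, oncologic, psychological and post-COVID conditions may well differ in later sick leave whatever their care planning. A one-arm model would show that gap and, under the stated aim, it would be read as a difference in who benefits. The reverse can also happen: a real difference in benefit can be cancelled by an opposite prognostic gap. What is at stake is the interpretation of the planned subgroup results.

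**Working it through.** **The plan's own figure.** Inputs from {14}: "a difference of 34 days of incapacity to work"; "assuming that the common standard deviation is 90 days using a two-group" *t*-test; 5% two-sided; "A sample size of 149 patients in each group will have 90% power"; about 15% loss. The two-sample *t*-test needs 148.2 per group, rounded up to 149, with power 0.90 at 149. Then 149/0.85 = 175.3, rounded up to 176 per arm, or 352 in total. The sample size reproduces. The article gives no figure for the subgroup analysis.

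**What the one-arm coefficient estimates.** Let T be treatment (0/1) and G a subgroup indicator, with mean outcome a + bT + cG + dTG.
- Control arm: the difference between subgroups is c (prognosis).
- Intervention arm: the difference between subgroups is c + d.
- Heterogeneity is d alone.

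The intervention arm yields c + d and nothing that isolates d. A larger sample does not help.

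**Diagnosis contrast, true interaction zero.** SD 90 and 149 analysed per arm are the plan's figures. Four equal diagnosis groups are assumed, so 149/4 = 37.25 per group per arm. The article gives no prognostic gap, so a range is shown.
- SE of a two-diagnosis contrast within one arm = 90 × √(2/37.25) = 20.9 days.
- Probability of a significant result ≈ P(Z > 1.96 − gap/20.9), plus a negligible opposite tail.

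| Assumed prognostic gap | Gap/SE | Declared heterogeneity, one arm | Interaction test |
|---|---|---|---|
| 15 days | 0.72 | about 11% | 5% |
| 34 days | 1.63 | about 37% | 5% |
| 60 days | 2.88 | about 82% | 5% |

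**Binary factor, by simulation.** This used 10,000 trials per scenario, 149 per arm, SD 90, a main effect of −34 days and an assumed split of about 50:50.
- No true heterogeneity, prognostic gap 15, 34 or 45 days: the one-arm analysis is significant in 17%, 64% and 87% of trials; the interaction test in about 5% each time.
- True heterogeneity −34 days, prognostic gap +34 days: the one-arm estimate averages about 0 and is significant in 5%. The interaction estimate averages about −34 and is significant in 36%.

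These rates exceed those in the table at the same gap because a 50:50 split leaves about 74.5 patients per subgroup, with SE 90 × √(2/74.5) = 14.7 days.

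**Precision of the correct analysis.**
- Main effect: SE = 90 × √(2/149) = 10.4 days.
- Interaction, 50:50 subgroup: SE = 90 × √(4/74.5) = 20.9 days; 95% CI half-width 1.96 × 20.9 ≈ 41 days; power for a 34-day interaction about 37%. The detectable interaction is about 58 days at 80% power and 68 days at 90%.
- Interaction between two of four equal diagnosis groups: SE = 90 × √(4/37.25) = 29.5 days, so precision is lower still.

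**The case against.** The strongest reply is that the sentence is loose drafting. Section {20a} says that all analyses follow a modified intention-to-treat approach by randomised assignment, which fits poorly with dropping an arm. Section {20c} uses the same term for the allocation variable. The stated aim itself presupposes a contrast between arms, and under {17a} the statistical analysis plan is finalised before unblinding and could set out interaction terms. This lowers the certainty that the analysis would really be run in one arm. It does not rescue the text. The predominant use of the term is for the single arm, no other section corrects the sentence, and a statistician following it would leave the controls out. The point is also not about missing detail: a method is stated, and it cannot reach its stated aim.

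A reader might infer that the one-arm coefficient measures prognosis and nothing else. That goes too far. It is prognosis plus interaction, and is pure prognosis only when the interaction is zero.

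A reader might also take 82% as the error rate. It belongs to one assumed gap of 60 days, about 1.8 times the planning difference of 34 days; smaller gaps give much lower figures.

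Finally, the correct analysis is weak. With about 37% power for a 34-day interaction at full size, and recruitment ended early for low numbers (Trial status), it will seldom settle anything. That is a reason for an exploratory label, not for keeping a model that estimates something else.

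**Conclusion.** As written, the subgroup analysis confounds prognosis with heterogeneity and cannot deliver its stated aim. That conclusion is algebraic and needs no assumption about numbers.

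The size of the problem does depend on assumptions. With no true interaction, false declarations run from about 11% to 82% for prognostic gaps of 15 to 60 days between two of four equal diagnosis groups. The gap means the difference remaining after whatever covariates the model adjusts for, which the article does not specify. The calculations use SD 90 throughout and ignore covariate adjustment and clustering by physician.

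This should be fixed, but it is not a fundamental defect of the trial. A reader might infer that the main result or the trial's use for planning care is compromised. The documents do not support that: this is an additional analysis with no confirmatory claim attached, the primary and secondary between-group comparisons do not depend on it, and the sample size reproduces.

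**What to change.** Replace the sentence in {20b} with wording such as:

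> Heterogeneity is assessed in both arms, in the same analysis population as the primary model (with the multiple-imputation sensitivity analysis), by adding treatment-by-age, treatment-by-gender and treatment-by-main-diagnosis interactions, one at a time, to the primary model. The diagnosis model also includes the main effect of main diagnosis. Interaction estimates and subgroup-specific between-group differences are reported with 95% confidence intervals and labelled exploratory.

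Two details matter. The primary model in {20a} has no diagnosis term. Adding only the interaction would force all control diagnoses to share one mean and bring the one-arm problem back, so the main effect is needed. The population should also be named as that of the primary model, because the main analysis excludes cases with missing data and so does not cover everyone randomised.

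Any model fitted within one arm should be called prognostic or descriptive.

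The cost is wording only. Section {18a} lists age, gender and main diagnosis among the data collected from patients, without restriction by arm. The drawback is low precision, which will fall further after the early end of recruitment.
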